### Definition of absence of AKI

Subjects will be considered not to have AKI if they meet the following criteria. For adult participants, non-AKI status will be defined as having both <20% relative increase and an absolute increase ≤0.2 mg/dL (18 μmol/L) in peak inpatient serum creatinine compared with baseline outpatient serum creatinine. For pediatric participants, non-AKI status will be defined as <50% relative increase in peak inpatient serum creatinine compared with baseline serum creatinine.

### Initial screening and enrollment of participants

Subject recruitment will vary by participating site and among adult versus pediatric participants, in accordance with requirements of local institutional review boards' guidelines and the requirements of sites within each Clinical Research Center network. As described above, all pediatric patients undergoing cardiac surgery requiring cardiopulmonary bypass at the two pediatric TRIBE-AKI sites will be screened for enrollment into ASSESS-AKI. Enrollment of ASSESS-AKI pediatric participants will occur post-operatively during the index hospitalization. During this first inpatient visit of enrolled children, baseline clinical data and quality of life questionnaires will be administered and 1 blood and urine specimen obtained within the first four post-operative days will be stored for future biomarker testing.

Among adult participants, we will enroll a parallel matched cohort of patients with and without AKI (Figure 2). Adult patients with AKI will be identified during the index hospitalization and screened for initial eligibility. During this inpatient visit, enrolled AKI patients will undergo urinalysis with microscopy through the hospital clinical laboratory and provide at least one sample of blood and urine for future biomarker testing within 96 hours of the episode of AKI.

**Figure 2 F2:**
[figure not shown]
**Summary of identification and enrollment approach for AKI and Non-AKI participants**. The figure applies to adult participants only. Any eligible pediatric subject undergoing cardiopulmonary bypass-requiring cardiac surgery is approached for participation during the inpatient phase.

Given the matched parallel cohort design, we will identify and enroll a sample of hospitalized adult patients who did not appear to suffer an AKI episode and who are matched in a minimum 1:1 AKI:non-AKI ratio, with each non-AKI subject individually matched to their corresponding AKI subject on the following set of key confounding characteristics: Clinical Research Center and presence of baseline chronic kidney disease using an CKD-EPI[19] equation-estimated GFR threshold of <60 ml/min/1.73 m^2^. In addition, we will further attempt to match on the presence or absence of clinical cardiovascular disease, presence or absence of diabetes mellitus, category of baseline eGFR (15-29, 30-44, 45-59, 60-89, 90-150 ml/min/1.73 m^2^), adult age category (18-39, 40-49, 50-59, 60-69, 70-79, 80-89 years), and hospital location where AKI episode occurred (ICU versus non-ICU).

### Follow-up visits and retention strategies

The follow-up visit and contact schedule are summarized in Table 2. All recruited participants will be invited to an in-person baseline study visit at 3 months after the AKI episode for AKI participants or 3 months after hospital discharge for non-AKI participants. Participants will return annually for in-person follow-up visits. Participants will be contacted by telephone at the 6-month intervals between clinic visits to obtain information on study events, or updates on general health and contact information.

**Table 2 T2:** Summary of visit schedule and study components for the ASSESS-AKI Study

Schedule	Inpatient	Baseline	Year 1		Year 2		Year 3		Year 4	
Months	0	3	6	12	18	24	30	36	42	48
Type of Contact	Visit	Visit	Phone	Visit	Phone	Visit	Phone	Visit	Phone	Visit
Consent for inpatient visit and specimen collection	●									
Consent for long-term follow-up		●								
Update contact info	●	●	●	●	●	●	●	●	●	●
Inpatient medications	●									
Inpatient risk factors for AKI	●									
Outcome Events		●	●	●	●	●	●	●	●	●
Outpatient medications		●	●	●	●	●	●	●	●	●
Urinalysis with microscopy (adults)	●									
Urine dipstick (adults)		●		●		●		●		●
Height and weight		●		●		●		●		●
Blood pressure		●		●		●		●		●
Questionnaires										
Sociodemographic characteristics	●	●								
Lifestyle habits		●		●		●		●		●
Medical History		●		●		●		●		●
Quality of life and functional status		●		●		●		●		●
Cognitive function (adults)		●		●				●		
Electrocardiogram (adults)		●		●		●		●		●
Collect specimens for storage in biorepository	●	●		●		●		●		●
Random urine sample	●	●		●		●		●		●
Blood for DNA		●								
Serum		●		●		●		●		●
Plasma-EDTA	●	●		●		●		●		●
Plasma-citrate		●		●		●		●		●

Consistent with other cohort studies (e.g., Atherosclerosis Risk in Communities Study,[20] Cardiovascular Health Study[21]), we project that approximately 3 to 5% of participants may be lost to follow-up annually. Multiple approaches will be used to prevent participant dropout. The National Death Index will be searched periodically for all participants lost-to-follow-up to ensure complete vital status information. We will implement previously tested retention strategies to promote a high level of long-term participation. These will include free medical testing, semi-annual contact with participants via telephone calls, along with newsletters containing study updates and information about kidney disease, personalized mailings, and reimbursement of time and travel expenses.

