#### Exclusion criteria

Exclusion criteria were selected to balance the goal of maximizing representativeness of the cohort, clinical accuracy of AKI, and feasibility in achieving the project goals. These criteria are detailed in Table 1. The data sources used to ascertain information on these criteria include electronic and paper medical records, other electronic databases, and patient interviews.

**Table 1 T1:** Inclusion and exclusion criteria for the ASSESS-AKI Study.

Inclusion criteria	Exclusion Criteria
Adult participants aged 18 years to 89 years.	Inability to provide informed or surrogate consent.
Children aged greater than one month to less than 18 years old at cohort entry.	Died prior to the three-month study visit.
Documented "baseline" serum creatinine defined as the outpatient, non-emergency department test value nearest to the index hospitalization within 7 and 365 days prior to admission using an IDMS-traceable serum creatinine assay.	Incarcerated, institutionalized, or otherwise unable to participate in the study within a home, community, or clinical setting.
In the TRIBE-AKI consortium, pre-operative serum creatinine results from an IDMS-traceable assay obtained within seven days before cardiac surgery can be used to define "baseline" kidney function for the subset of participants who are undergoing non-urgent cardiac surgery.	Enrolled in an active interventional study at the three-month in-person study visit.
For pediatric participants in TRIBE-AKI, a pre-operative serum creatinine concentration measured in the local hospital clinical laboratory among patients scheduled for elective cardiac surgery.	Actively pregnant or breastfeeding. Prior chronic hemodialysis, peritoneal dialysis (lasting ≥three months), or estimated GFR <15 ml/min/1.73 m2 not receiving renal replacement therapy. History of solid organ and/or hematopoietic cell transplants.
	Acute glomerulonephritis diagnosed clinically or by biopsy.
	Clinically significant urinary tract obstruction, confirmed by imaging.
	Hospitalization involving acute nephrectomy.
	History of multiple myeloma.
	Hepatorenal syndrome.
	Metastatic cancer or systemic cancer receiving active treatment.
	New York Heart Association Class IV heart failure prior to index admission.
	Predicted survival of 12 months or less as determined by the participant's treating physician or Clinical Research.
	Center Principal Investigator.

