	AKI participants who remain hospitalized 90 or more days after the AKI episode.
	ESRD at the time of the three-month study visit.
	Unable to provide at least 1.5 mL of plasma for adults at the Inpatient visit.
	Unable to provide at least 3 mL of urine for adults at the Inpatient visit.
	Unable to provide at least 10 mL of blood for adults and 1 mL of blood for children at the three-month visit.

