### Collection of study data

At the outpatient visit at 3 months following the index hospitalization, adult participants will be screened again for eligibility and eligible persons will have consent obtained for long-term follow-up (Table 2). Pediatric participants will have had consent for long-term follow-up visits obtained during the index hospitalization. Information will be collected on detailed sociodemographic information, lifestyle habits, medical and family history, quality of life, current medication use, quality of life and functional status (SF-12v2™ Health Survey[22] in adults, PedsQL Generic and Cardiac modules in children),[23] cognitive function (Modified Mini-Mental Status Examination,[3MS][24] and Trails B[25]), anthropometric measures (weight, height), and resting blood pressure and heart rate. In addition, blood specimens for DNA, sera and plasma as well as a random urine sample will be obtained for local urine dipstick testing (CLINITEK Status^® ^Analyzer, Siemens, New York, NY). Sera, plasma and urine samples will be collected annually and stored for subsequent measurement of renal and cardiovascular-related biomarkers related to multiple pathways involving early AKI. The list of all the different biological specimen types that are being collected at each visit and will be stored in the NIDDK biorepository are given in Table 2.

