#### Development of ESRD

Development of ESRD after the 3 month follow-up visit will be defined as any of the following: (1) peritoneal dialysis or hemodialysis treatment at least once a week for at least 12 consecutive weeks, (2) receipt of a kidney transplant and/or (3) death while receiving dialysis.

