### Statistical approach and power

The primary outcomes for the study are time-to-event outcomes, such as time to death, a renal event or a clinical cardiovascular event. Some of these events will be known exactly on a continuum and could be right-censored. Exact dates for the occurrence of some of the events, however, may only be known to occur within a specific time interval t_k_, k = 1, 2, 3, 4, 5 (t_1 _= 0-3 months, t_2 _= 3-12 months, t_3 _= 12-24 months, t_4 _= 24-36 months, t_5 _= 36-48 months). The endpoints of these five time intervals correspond to the planned in-person study visits. Therefore, the statistical analyses in these situations will invoke continuous time-to-event models that account for right-censored and interval-censored data.

The hazard function for a continuous time-to-event outcome is of the form

$$\lambda_{\text{ijk}}(\text{t};{\text{x}}_{\text{ijk}})=\lambda_{0}(\text{t})\exp({\text{x}}_{\text{ijk}}\beta )$$

where

(a) λ_ijk_(t; x_ij_) is the hazard function at time t with covariate vector x_ijk _for the k^th ^member of the j^th ^matched set within the i^th ^site, j = 1, 2,...,n_i_, and k = 0 (non-AKI), 1 (AKI),

(b) λ_0_(t) is the baseline hazard function,

(c) β is an unknown parameter vector, and

(d) x_ijk _is a vector of regressors of interest.

The regressors that will appear in x_ijk _for the primary statistical analyses are as follows using as examples different variables: binary indicator variables at month 0 for non-AKI/AKI status, CKD status, gender, Hispanic ethnicity, cardiovascular disease status, diabetes status and sepsis status; ordinal variables at month 0 for racial group (0 = white/European, 1 = Black/African American, 3 = Asian/Pacific Islander, 4 = Native American, 5 = Other/Admixed), eGFR (0 = 15 to 29, 1 = 30 to 44, 2 = 45 to 59, 3 = 60 to 89, 4 = 90-150) and albumin-to-creatinine ratio (0 = <0.15, 1 = 0.15 to 0.5, 2 = >0.5 to 1.0, 3 = >1.0 to 3.0, and 4 = >3.0), age (0 = 1 to 17, 1 = 18 to 39, 2 = 40 to 49, 3 = 50 to 59, 4 = 60 to 69, 5 = 70 to 79, 6 = 80 to 89).

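### The 3-month visit that gates cohort entry is timed from the AKI episode in AKI participants but from hospital discharge in controls, and another section times it differently again

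*Protocol article*

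**What the plan says.** Three sections of the protocol article fix when the 3-month visit happens.

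- **Follow-up visits and retention strategies** gives each group its own anchor: an "in-person baseline study visit at 3 months after the AKI episode for AKI participants or 3 months after hospital discharge for non-AKI participants".
- **Collection of study data** gives all adults one anchor: "At the outpatient visit at 3 months following the index hospitalization, adult participants will be screened again for eligibility".
- **Table 1 (exclusion criteria)** removes "AKI participants who remain hospitalized 90 or more days after the AKI episode". This counts from the episode, in line with the first section, and applies to AKI participants only.

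The visit is also the gate into the cohort. Table 1 excludes anyone who "Died prior to the three-month study visit" and anyone with "ESRD at the time of the three-month study visit". The ESRD outcome starts at the same point: "Development of ESRD after the 3 month follow-up visit will be defined as any of the following". The sample size in Statistical approach and power is counted at the 3-month visit. That section also ties the analysis intervals to the visits: "The endpoints of these five time intervals correspond to the planned in-person study visits".

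**The concern.** The study exists to isolate the effect of AKI, yet the timing of the visit depends on AKI status. Two things follow.

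1. **Entry.** Survival and freedom from ESRD are required over windows of different length. Two people with the same course after discharge can be treated differently: one contributes an outcome, the other is never enrolled.
2. **Measurement.** Quality of life, cognition, blood pressure and the first outpatient biomarker samples are taken closer to the acute illness in AKI participants. A month-3 contrast between groups then mixes AKI with time since discharge.

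Both are tied to exposure, so a larger sample does not reduce them. The matching list (centre and CKD, with attempts on cardiovascular disease, diabetes, eGFR category, age and ICU location) does not include length of stay. The regressors listed for the primary analyses include neither length of stay nor days since discharge. Matching on stay would still leave the two anchors different.

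**Working it through.** **The plan's own figure.** The article states more than 80% power with 1,200 participants and 15% withdrawal. With 600 × 0.85 = 510 per group and a pooled two-proportion test at two-sided 0.05:

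- AKI rate 30%, relative risk 1.35, so control rate 0.30/1.35 = 22.2%: power 80.8%.
- AKI rate 10%, relative risk 1.90, so control rate 0.10/1.90 = 5.26%: power 81.4%.

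The statement reproduces. It does not depend on the visit anchor and is not in dispute here.

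**Size of the gap.** Take 3 months as 90 days. Let L be the days from the AKI episode, or from the equivalent hospital day in the matched control, to discharge.

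- AKI visit: 90 days after the episode, which is 90 − L days after discharge.
- Control visit: 90 days after discharge, which is 90 + L days after the equivalent hospital day.
- Gap on either scale: L days.

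The article does not give L, so 14 and 30 are assumed values; 89 is the most that Table 1 allows.

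| L (days) | AKI visit, days after discharge | Control visit, days after discharge |
|---|---|---|
| 14 | 76 | 90 |
| 30 | 60 | 90 |
| 89 | 1 | 90 |

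**Effect on entry, with no hazard assumption.** Take L = 20 and a death 80 days after discharge. The AKI participant's visit fell due at day 90 − 20 = 70, so the death is an outcome. The control's visit falls due at day 90, so the same death is an exclusion.

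**Effect on the hazard ratio (illustration).** Assume no AKI effect, the same L in both members of a pair, and a Weibull cumulative hazard H(t) = t^k, with t counted from the episode or equivalent hospital day. The artefact to month 48 (day 1461) is

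[H(1461) − H(90)] / [H(1461 + L) − H(90 + L)],

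and to month 12 the same with 365 in place of 1461. For k = 0.5 and L = 30: (38.22 − 9.49)/(38.61 − 10.95) = 28.74/27.66 = 1.039.

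| L (days) | Months 3-12, k = 0.7 | Months 3-12, k = 0.5 | Months 3-48, k = 0.7 | Months 3-48, k = 0.5 |
|---|---|---|---|---|
| 7 | 1.011 | 1.019 | 1.005 | 1.010 |
| 14 | 1.022 | 1.038 | 1.010 | 1.019 |
| 30 | 1.045 | 1.078 | 1.021 | 1.039 |

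With k = 1 (constant hazard) every entry is 1.000. With a common anchor the systematic gap is zero.

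**The case against.** Several points on the other side are sound.

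- **Time zero is not stated.** The anchors concern a visit. Table 2 labels month 0 as inpatient for everyone, the regressors are taken at month 0, and some event dates are known exactly. A reader might infer from the visit-based intervals that the hazard models start the clock at different dates in the two groups. The article does not say so, and the precise time zero may be set in a full protocol or SAP that is not shown.
- **Renal change has a different reference.** A reader might take the month-3 visit, because it is labelled baseline, as the reference for loss of eGFR. The section on baseline kidney function and the Discussion tie renal change to the pre-admission creatinine, which both groups have.
- **The anchor is a trade-off.** Counting from the episode holds time since injury constant within the AKI group, and controls have no episode. Figure 2, which summarises enrolment, is not visible, so a rationale cannot be ruled out.
- **The wording conflict may be loose drafting.** The data-collection sentence describes the visit in passing; the follow-up section sets the schedule, and Table 1 agrees with it.

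The first two limit the claim and are accepted. The third explains the AKI anchor but does not justify a different one for controls, who can be given the matched equivalent hospital day. On the fourth, sites could still schedule AKI visits by either sentence, so the two need reconciling. An analysis plan could adjust for timing, but who enters is decided by the visit rule itself.

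**Conclusion.** The point holds. The visit that admits participants and starts ESRD ascertainment is timed by exposure. AKI participants enter and are measured L days sooner after discharge than controls, with L up to 89 days permitted. The expected direction is to make the AKI group look worse.

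The size is modest for long-term hazard ratios: about 0.5 to 4% over months 3-48 for L of 7 to 30 days, and none if the hazard is constant. It is larger for early events (about 1 to 8% over months 3-12), and the month-3 measures carry the whole gap. These figures rest on assumed stays and an assumed Weibull shape of 0.5 to 0.7.

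A reader might be tempted to go further. If the hazard is assumed to halve every 45 to 90 days, the hazard at the moment of entry differs by a factor of 2^(L/half-life), or 1.26 to 1.59 for L = 30, which seems large beside the detectable relative risk of 1.35. The documents do not support that comparison. The half-life is an assumption, and an instantaneous hazard at entry is not the same quantity as a relative risk built on cumulative event rates of 10 to 30%.

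**What to change.** 1. Reconcile the follow-up and data-collection sections to one anchor for both groups: either discharge for both, or the AKI episode day with the matched equivalent hospital day for controls.
2. Apply the 90-day prolonged-stay exclusion to both groups, counted from an in-hospital date such as index admission or the matched hospital day. Counted from discharge it would have no meaning.
3. State one common time zero for the hazard models, with delayed entry at the visit, so that each person is at risk only from the date they could be observed.
4. For visits already held, adjust month-3 measures for days since discharge.

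**Cost.** A short amendment to the visit schedule and to one row of Table 1, plus re-dating of participants already seen. Some visits shift by the length of the post-AKI stay. Under a discharge anchor, time since injury varies within the AKI group; under the hospital-day anchor, each control needs an assigned date. Later adjustment cannot bring back controls already excluded, which favours making the change early.

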### Collection of study data

At the outpatient visit at 3 months following the index hospitalization, adult participants will be screened again for eligibility and eligible persons will have consent obtained for long-term follow-up (Table 2). Pediatric participants will have had consent for long-term follow-up visits obtained during the index hospitalization. Information will be collected on detailed sociodemographic information, lifestyle habits, medical and family history, quality of life, current medication use, quality of life and functional status (SF-12v2™ Health Survey[22] in adults, PedsQL Generic and Cardiac modules in children),[23] cognitive function (Modified Mini-Mental Status Examination,[3MS][24] and Trails B[25]), anthropometric measures (weight, height), and resting blood pressure and heart rate. In addition, blood specimens for DNA, sera and plasma as well as a random urine sample will be obtained for local urine dipstick testing (CLINITEK Status^® ^Analyzer, Siemens, New York, NY). Sera, plasma and urine samples will be collected annually and stored for subsequent measurement of renal and cardiovascular-related biomarkers related to multiple pathways involving early AKI. The list of all the different biological specimen types that are being collected at each visit and will be stored in the NIDDK biorepository are given in Table 2.

### Biomarkers

A major goal of ASSESS-AKI is to evaluate the utility of urine and blood biomarkers for improving the diagnosis and risk stratification after a hospitalized episode of AKI. Given rapid and ongoing advances in the discovery of putative novel biomarkers for AKI,[18] the biomarkers to be evaluated within ASSESS-AKI will be prioritized based on the currently available evidence at the time of testing. The initial preliminary set of biomarkers includes those with the strongest clinical evidence base as markers of early AKI and will be measured in all study participants. Given the current data supporting the use of these markers for the detection of AKI, it will be important to know whether these markers predict short or long term outcomes. This set will include urine biomarkers (IL-18,[26] NGAL,[27] KIM-1,[28] cystatin C,[29] L-FABP[30] and NAG[31]) and blood biomarkers (serum cystatin C,[32] serum NGAL[33] and plasma IL-6[34]).

### Renal outcomes

#### Kidney function measurement

The primary renal outcome is the change in kidney function during follow-up. Kidney function will be defined before and after an AKI episode (as well as among those without AKI) using outpatient serum creatinine concentration measurements. Given the known limitations of using serum creatinine alone as a measure of kidney function,[35] except for its use in defining an episode of AKI per the criteria described previously, we will use the CKD-EPI equation to estimate GFR using an IDMS-traceable serum creatinine assay among all adult study participants. For pediatric participants, we will estimate GFR using the recommended Schwartz formula[36] based on serum creatinine values measured in local laboratories using the same assays for baseline and follow-up measurements within those sites. Urine albuminuria will be measured using a spot albumin-to-creatinine ratio [37].

